## Abstract

**Background:**

Intensive therapies based on motor skill learning have been widely used in stroke rehabilitation for improving upper extremity abilities, demonstrating significant improvements in arm function and daily life activities. Based on the same therapeutic principles of motor skill learning, hand and arm bimanual intensive therapy including lower extremities (HABIT-ILE) was developed focusing on bimanual coordination and constant concomitant stimulation of trunk control and lower extremities. However, the implementation of such high-dosage interventions in stroke rehabilitation might face barriers due to limited accessibility and high resource requirements. Delivering HABIT-ILE therapy at home (HABIT-ILE@home) via telerehabilitation may reduce logistical barriers while maintaining efficacy. In addition, the added value of a 9-week specific follow-up program will be tested after high dosage interventions.

**Objective:**

The first randomized controlled trial (RCT1) aims to evaluate the noninferiority of a high-dosage HABIT-ILE@home program compared to its on-site counterpart. The second randomized controlled trial (RCT2) aims to test the superiority of a 9-week specific HABIT-ILE@home follow-up vs a nonspecific home program.

**Methods:**

A total of 48 adults with chronic stroke will be randomized to either HABIT-ILE@home or HABIT-ILE on-site group (RCT1, 65 hours over 2 weeks). HABIT-ILE@home will follow the same principles as HABIT-ILE on-site but will be delivered by caregivers with remote supervision by trained therapists and the use of a dedicated telerehabilitation device to facilitate intervention delivery and remote monitoring (ie, REAtouch Lite; Axinesis). All participants will then participate in a HABIT-ILE@home follow-up program or nonspecific follow-up (RCT2, 45 hours over 9 weeks). Primary outcomes will be the change in Fugl-Meyer Assessment (FMA), while secondary outcomes include feasibility and adherence questionnaires, upper and lower extremity motor function assessments, daily activities, and quality of life questionnaires. Assessments will be performed before (T0) and after (T1) the 2 weeks of high dosage intervention, followed by an assessment after the 9-week follow-up (T2).

**Results:**

Recruitment for the trial started in March 2023 and ended in March 2025, and data collection has been completed for this study. Data analysis is planned to start early 2026; we expect to submit the results for publication in spring 2026.

**Conclusion:**

This study will provide evidence on the feasibility and efficacy of delivering HABIT-ILE through a home-based telerehabilitation model for adults with chronic stroke. Demonstrating noninferiority of HABIT-ILE@home compared to on-site therapy would support wider accessibility to intensive rehabilitation while reducing logistical and human resource constraints. Additionally, showing the added benefit of a structured follow-up could emphasize the importance of continuity of care to sustain and enhance motor recovery after intensive interventions.

## Introduction

### Background

The global lifetime risk of stroke in the adult population is 24.9% [1]. Stroke is the second leading cause of death and the primary etiology of motor disability in adults worldwide [2]. After a stroke, patients experience variable acute symptoms depending on the type, location, and size of the brain lesions: hemiparesis, which often causes partial or complete inability to use one upper limb, spasticity, loss of independent walking, chronic pain, alterations of sensations, and visuospatial neglect [3,4]. It is important to note that some of these symptoms may become chronic. The long-term consequences of the pathology, particularly the motor impairments, can lead to difficulties in daily activities and a lower quality of life [5,6].

Rehabilitation plays an important role in reducing the impact of symptoms and in improving the quality of life of stroke patients. A wide variety of rehabilitation interventions are available, including strength or manual dexterity training, neuromuscular stimulation, balance exercises, walking and task training, and stretching of the affected side [7]. The most effective interventions identified in the literature are those based on the principles of motor skill learning, such as constraint-induced movement therapy (CIMT), hand-arm bimanual intensive training, bilateral arm training, and high dose repetitive task practice [8-11]. These therapies have demonstrated significant improvement in upper extremity functions and activities of daily living [12-15]. More recently, hand and arm bimanual intensive therapy including lower extremities (HABIT-ILE) has been developed with a focus on bimanual coordination training with stimulation of postural control and lower extremities [16]. In adults with stroke, the implementation of a HABIT-ILE training is under investigation through a randomized controlled trial with expectations of similar improvements [17]. Although no results on the efficacy of HABIT-ILE in stroke patients are currently available, improvements similar to those observed in upper extremities with other intensive therapies based on motor skill learning are expected.

HABIT-ILE is usually organized through a 2-week on-site camp. Although this high therapeutic dosage is one of the ingredients necessary for its efficacy, it can also be considered an obstacle to the implementation of HABIT-ILE in clinical practice. As the number of locations offering HABIT-ILE therapy is currently limited, patients and their families often have to travel long distances to reach the therapy site and find accommodation for the duration of the treatment, and those unable to meet these burdens will not have access to therapy. The organization of HABIT-ILE sessions on-site is also challenging, as it requires specialized facilities, extensive equipment, and a large number of trained therapists (ie, one per participant), in a context where there is a lack of therapists qualified to administer this type of therapy. Additionally, public health crises such as the COVID-19 pandemic have demonstrated how vulnerable such therapy models can be, as they can be significantly disrupted by global health emergencies. These constraints are not specific to HABIT-ILE but are shared by other intensive motor skill learning-based interventions and contribute to limiting their dissemination in routine practice [18,19]. To overcome these potential barriers and improve the accessibility of HABIT-ILE, we propose a telerehabilitation modality.

Besides intensive interventions, access to outpatient therapies after stroke is sometimes limited, especially in rural areas [20]. Although some motor skills acquired during intensive motor skill learning therapies are maintained in the long term [21], some functional goals or newly acquired motor abilities might be difficult to transfer to daily life directly after a camp. The long-term and additional effects of such intensive interventions could be enhanced with a specific follow-up intervention focusing on the potentiation of the newly acquired abilities and their transfer in daily life. Based on this assumption, we aim to investigate the efficacy of a follow-up program of HABIT-ILE therapy at home (HABIT-ILE@home) in adults with stroke after the completion of intensive HABIT-ILE intervention (either on-site or at home).

### Aims and Hypotheses

This protocol comprises 2 randomized controlled trials (RCTs), hereafter referred to as RCT1 and RCT2, conducted in the same cohort of 48 adults with chronic stroke. The first trial (RCT1) aims to test whether a 2-week high-dosage HABIT-ILE telerehabilitation program (HABIT-ILE@home) is noninferior to a 2-week high-dosage on-site HABIT-ILE camp in improving motor function. We hypothesize that both interventions will lead to significant improvements in motor function, activities, and participation, and that the HABIT-ILE@home group will be noninferior to the on-site group when comparing changes from baseline to postintervention (T1-T0). We further hypothesize that HABIT-ILE@home will demonstrate higher self-perceived burden for caregivers but will show acceptable feasibility, adherence, and perceived efficacy.

The second trial (RCT2) aims to evaluate whether a structured 9-week specific HABIT-ILE@home follow-up program is more effective than a dose-matched nonspecific home-based follow-up in maintaining and further enhancing the improvements obtained after the intensive phase. We hypothesize that, over the follow-up period (T2-T1), participants allocated to the specific HABIT-ILE@home follow-up will show superior retention and/or additional improvements in motor function, activity performance, and social participation compared with those receiving the nonspecific follow-up. We further hypothesize that HABIT-ILE@home follow-up will demonstrate higher self-perceived burden for caregivers but will show acceptable feasibility, adherence, and perceived efficacy. All outcomes will be assessed at baseline (T0), immediately after the intensive 2-week intervention (T1), and after the 9-week follow-up period (T2).

## Methods

### Ethical Considerations

The study was approved by the Hospital-Faculty Ethics Committee of Saint-Luc – UCLouvain, Belgium (clinical trial number: B4032022000142) and was registered on ClinicalTrials.gov (NCT05727111) on February 2, 2023. Participants were informed by means of a comprehensive information document and signed an informed consent form. All data collected for this study will be treated anonymously. Compensation for research-related harm, if applicable, will be covered according to the institutional insurance arrangements in place for this study. Written consent for the use of data, including images and videos, was obtained from the participants, or from their parents or legal guardians in the case of minors. The data will be anonymized using allocation codes for analysis after both RCTs.

### Study Design

This study consists of 2 sequential, 2-arm, parallel-group pragmatic, single-blind RCTs conducted within the same cohort of adults with chronic stroke. RCT1 is a noninferiority trial comparing a 2-week high-dosage HABIT-ILE@home program with a dose-matched on-site HABIT-ILE camp (allocation ratio 1:1). RCT2 is a superiority trial comparing a 9-week specific HABIT-ILE@home follow-up to a dose-matched non-specific home-based follow-up. Randomization will be performed using pairwise randomization, and outcome assessors are blinded to group allocation. All evaluations will occur at baseline (T0), postintensive intervention (T1), and after the follow-up period (T2).

### Patient and Public Involvement

Before this RCT, a pilot HABIT-ILE@home study was conducted in which participants and caregivers completed questionnaires on feasibility, acceptability, and burden; their feedback was used to modify the current study protocol and enhance several components of the HABIT-ILE@home intervention. In the present trial, participants’ perception is gathered through completing satisfaction and burden questionnaires at the end of each intervention phase.

### Participants and Setting

A total of 48 participants with chronic stroke will be recruited from Belgium and surrounding countries through mailing, spontaneous applications, social networks, physicians, physiotherapists, occupational therapists, and hospitals. Participants will be considered eligible if they meet the following criteria: time since stroke of more than 6 months, ages 18 years and older at inclusion, ability to interact, and understand simple instructions for completing assessments and therapy, ability to voluntarily initiate minimal movement of the affected upper extremity (eg, observable slight minimal movement in either shoulder, elbow, wrist, or fingers). A caregiver must also be available for 6.5 hours per day over 2 weeks for the needs of the high-dosage HABIT-ILE@home intervention (RCT1) and for the duration of follow-up programs (RCT2). Participants will be ineligible if one of the following criteria is present: botulinum toxin injections, orthopedic surgery, or another intensive therapy during the 3 months before the first assessment (T0) or during the study period. Additionally, participants will not be included if they are pregnant or present uncontrolled seizures or other uncontrolled health issues such as heart or renal failure. Cognitive function will be assessed at baseline using the Montreal Cognitive Assessment. This measure will only serve as a descriptor, not for eligibility or outcomes. All assessments will be conducted on the UCLouvain premises in Brussels or Louvain-la-Neuve. This study will be reported following CONSORT guidelines (Figure 1).

**Figure 1. F1:**
[figure not shown]
CONSORT (Consolidated Standards for Reporting Trials) flowchart. ACTIVLIM: Activity Limitations Questionnaire; 6MWT: 6-minute walk test; BBT: box and block test; CaSM: Confidence After Stroke Measure; COPM: Canadian Occupational Performance Measure; FMA: Fugl-Meyer Assessment; HADS: Hospital Anxiety and Depression Scale; Mini-BESTest: Mini Balance Evaluation Systems Test; MoCA: Montreal Cognitive Assessment; mRS: modified Rankin scale; PILS-Stroke: Participation In Life Situations - Stroke; SIS: Stroke Impact Scale; TUG: timed up and go test; WMFT: Wolf Motor Function Test.

### Randomization Process

For RCT1, randomization will be performed using pairwise randomization. Participants will first be paired according to lesion side, time since stroke, age, and modified Rankin Scale (mRS) level. Participants in each pair will then be randomized into one of the two groups using an online external blind electronic randomization system [22], which will provide the assignment only after pairing is completed. This procedure will ensure allocation concealment, as investigators will not be able to predict or influence the upcoming allocation. For RCT2, the same procedure will be repeated within each RCT1 allocation arm, such that participants previously assigned to HABIT-ILE@home or HABIT-ILE on-site will be again matched and randomized in the HABIT-ILE@home follow-up subgroup or the nonspecific follow-up subgroup.

### Sample Size

For RCT1, assessing the noninferiority of HABIT-ILE@home compared to HABIT-ILE on-site, the sample size was calculated using PASS (version 14.0.15; NCSS) for a noninferiority 2-tailed *t* test of the difference between two means. The primary outcome is the change in the upper extremity subscale of the Fugl-Meyer Assessment (FMA-UE) score from baseline to postintervention (T1-T0), with higher scores indicating better motor abilities. We defined the noninferiority margin (NIM) using a method that ensures both clinical and statistical relevance, rather than only relying on the minimal clinically important difference. We chose the NIM as 50% of the difference between the changes observed with the gold-standard treatment and an interventional control group. This method was chosen to provide a more stringent criterion for noninferiority, ensuring that any treatment deemed non-inferior demonstrates a real benefit for stroke patients. As no previous studies have investigated such changes after a HABIT-ILE intervention, the sample size calculation was based on the mean change observed after a CIMT intervention (+5.6 points at FMA-UE; SD 3.1) [13]. The non-inferiority hypothesis was defined as follows: the HABIT-ILE@home intervention will be considered noninferior if the improvement produced is no more than 2.8 points lower than that obtained with the on-site HABIT-ILE intervention on the FMA-UE. An α level of 0.05 and a 1-β level of 0.8 were used for calculation. Under these assumptions, sample size calculation defined a number of 17 participants per group, resulting in a total of 34 participants.

For RCT2, which assesses the superiority of the specific HABIT-ILE@home follow-up compared with the nonspecific follow-up, the sample size calculation was also based on the mean changes in the FMA-UE observed in the study of Bonifer et al [13] by adjusting the expected improvements to account for the lower number of therapy hours in RCT2. Scaled proportionally, a 45-hour program corresponds to an expected improvement of 2.8 points. Because both follow-up arms constitute active interventions, the superiority margin was set at 1.4 points (50% of the expected 45-hour gain), reflecting a meaningful difference between two active interventions. Consequently, 17 participants are needed per group, resulting in a total of 34 participants, with a α level of .05 and a 1-β level of .8. To ensure that the required number of participants complete both phases, we plan to recruit 48 individuals, corresponding to an anticipated attrition rate of about 30%. This conservative estimate was based on a previous study with a similar population and reflects the two-phase design and the substantial differences between intervention modalities, with participants enrolled before being informed of their allocation [17].

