#### RCT 1: HABIT-ILE@home vs HABIT-ILE on-Site Camp (2 Weeks)

Non-inferiority statistics will be used to compare the efficacy of the HABIT-ILE@home modality with the HABIT-ILE on-site camp modality. First, within each intervention arm, changes from baseline (T0) to postintervention (T1) will be evaluated for all outcomes. Depending on data normality, paired samples *t* tests or nonparametric equivalents will be applied. Then, the 95% CI of the difference between groups will be computed by comparing group differences in change scores using independent *t* tests or nonparametric equivalents. Noninferiority will be concluded if the lower bound of this interval is above the prespecified NIM. For all outcomes, NIM will be defined as 50% of the difference between the changes observed with a gold standard (ie, CIMT) and a control group [13].

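### The 2.8-point noninferiority margin for RCT1 does not follow from the plan's own rule: it is half of the CIMT group's change, with no control-group change subtracted

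*Protocol article*

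**What the plan says.** The protocol article states the margin rule twice. Under Sample Size: "We chose the NIM as 50% of the difference between the changes observed with the gold-standard treatment and an interventional control group". Under Statistical Analysis, RCT 1: "For all outcomes, NIM will be defined as 50% of the difference between the changes observed with a gold standard", with CIMT named as the gold standard, a control group as the other term, and the same cited study as the source.

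The input is given once: "the sample size calculation was based on the mean change observed after a CIMT intervention (+5.6 points at FMA-UE; SD 3.1". The resulting criterion is that the home group's improvement may be "no more than 2.8 points lower than that obtained with the on-site HABIT-ILE intervention on the FMA-UE".

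The Sample Size section presents the rule as stricter than relying on a minimal clinically important difference alone, and credits it with "ensuring that any treatment deemed non-inferior demonstrates a real benefit for stroke patients".

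The margin decides RCT1: noninferiority is concluded if the lower bound of the 95% CI for the difference between groups lies above it.

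**The concern.** The rule needs two numbers, the change with CIMT and the change in a control group. The article reports one and halves it. A within-group change contains whatever a control group would also have gained, such as practice on the test, regression to the mean and the effect of any other therapy. The rule subtracts the control change to remove those parts.

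If the control group improved, a margin of half the raw gain gives away more than half of the effect attributable to CIMT, and the stated purpose of the rule is lost. RCT1 has no usual-care or untreated arm, so the assurance of benefit rests on this historical margin. The sample size also rests on it: a smaller margin with the same number of patients means less power.

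**Working it through.** **Inputs.** From Sample Size: CIMT change 5.6, SD 3.1, margin 2.8, alpha 0.05, power 0.80, 17 per group. From Statistical Analysis, RCT 1: the decision uses a 95% CI. The control-group change, *c*, is not given; the values below are assumptions. The true difference between groups is taken as 0.

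**Step 1: reproduce the margin.** 0.5 × 5.6 = 2.8, exactly the stated figure. The rule is 0.5 × (5.6 − *c*), and setting this equal to 2.8 gives *c* = 0.

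**Step 2: check whether 5.6 could already be a net difference.** The article words it as the mean change after CIMT. The RCT2 paragraph of the same section uses the same study's changes, scales them by therapy hours to an expected improvement of 2.8 for 45 hours, and then halves that to 1.4 because both arms are active. That treats the figure as the gain in one arm.

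**Step 3: reproduce the sample size.** Normal approximation: n per group = 2 × (z_α + z_β)² × SD² / margin².
- One-sided 0.05: 2 × (1.645 + 0.842)² × 3.1² / 2.8² = 15.2, so 16. The exact t calculation also gives 16, and 17 per group has power 0.824. This roughly reproduces the stated 17.
- One-sided 0.025, which matches a 95% CI: 20 by the normal approximation, 21 by exact t. Power at 17 per group is 0.724.

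**Step 4: apply the rule with an assumed control change.** Power is from the noncentral t distribution with 2n − 2 degrees of freedom and noncentrality margin / (SD × √(2/n)). For n = 17, SD × √(2/17) = 1.063, so the noncentrality is 2.63, 2.16 and 1.69 for margins 2.8, 2.3 and 1.8.

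| Assumed control change *c* | Margin by the rule | 2.8 as share of (5.6 − *c*) | Power, 17 per group, one-sided 0.05 | Power, 17 per group, one-sided 0.025 | Power, 24 per group, one-sided 0.025 |
|---|---|---|---|---|---|
| 0 | 2.8 | 50% | 0.82 | 0.72 | 0.87 |
| 1 | 2.3 | 61% | 0.68 | 0.56 | 0.71 |
| 2 | 1.8 | 78% | 0.51 | 0.38 | 0.50 |

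The 24-per-group column is the best case, with all 48 recruits analysed.

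**Step 5: separate the two causes of lost power.** Reading down a column shows the effect of the margin. The step from 0.82 to 0.72 in the first row comes only from the alpha level and is a different matter.

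**The case against.** The strongest reply is that the article condenses a fuller protocol and the control change may be recorded there. If the cited study's control group did not change, 2.8 is what the rule produces; if it got worse, the rule would allow a wider margin. The word interventional makes a positive control change plausible but does not establish it, and the analysis section says only a control group. This stands against any statement about size. It does not remove the mismatch, because the article states a rule needing a subtraction and then shows a number with none.

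Stronger readings are tempting, and the documents do not support them:

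- A reader might infer that the margin is definitely too wide. That requires a control change above 0, which the article does not report.
- A reader might infer that home therapy could lose the whole controlled benefit and still pass. That requires a control gain of at least 2.8 points, half of the CIMT gain, and nothing in the article supports that value.
- A reader might blame the margin for power of 0.72 at 17 per group. That figure is for the unchanged 2.8 margin and reflects the 95% CI rule.
- A reader might count the use of CIMT data as an error. The article discloses it and gives the reason; the Background says "Although no results on the efficacy of HABIT-ILE in stroke patients are currently available".
- A reader might want noninferiority made conditional on the on-site arm's own improvement. That is another uncontrolled before-after change and would not repair the margin.

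**Conclusion.** The point holds as an inconsistency between the rule and the number that decides RCT1. As shown, 2.8 is half of a single-group CIMT change, and it agrees with the stated rule only if the control group's change was exactly zero. This conclusion needs no outside figure.

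The consequence is conditional. For control gains of 1 to 2 points the rule-based margin would be 2.3 to 1.8, and power with 17 per group would be 0.68 to 0.51 at one-sided 0.05, or 0.56 to 0.38 under the planned 95% CI. These figures assume SD 3.1, no true difference and the stated 17 per group.

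The claim that any noninferior treatment brings a real benefit is not supported as written, because the article does not show what share of a controlled effect the margin preserves.

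**What to change.** Before analysis starts and blind to results, issue a dated amendment that:

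1. reports the control-group change from the cited study, recomputes the margin as 0.5 × (CIMT change − control change), and replaces 2.8 with the result;
2. restates the power for the new margin under the 95% CI used for the decision.

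If the cited study has no usable control change, say plainly that 2.8 is half of an uncontrolled within-group CIMT change, and delete the statement that noninferiority ensures a real benefit.

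The work is one recalculation from a source already cited, plus the amendment. The Results section places data analysis in 2026, so there was still time when the article was written. Recruitment is closed, so the sample size stays as it is. If the control group improved, the stated power becomes less favourable and that loss cannot be recovered.

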## Discussion

### Principal Findings

Previous studies have shown that home-based telerehabilitation may be as effective as in-person therapies [56] with good treatment adherence [57]. Specifically, intensive interventions based on motor skill learning principles such as CIMT have shown similar effectiveness at home (both with or without a rehabilitation device) compared to in-person CIMT [19] or standard therapy [58]. Based on these previous results, we anticipate similar improvements when comparing HABIT-ILE@home and HABIT-ILE on-site camp within the first RCT.

However, there may be some challenges for participants to engage in such an intensive home intervention (short duration, high dosage), or even for a home follow-up intervention (longer duration, low to moderate dosage). The higher dosage of the therapy (65 hours) compared to previous studies may be more difficult for participants and caregivers to manage in terms of tiredness and motivation. Nevertheless, intrinsic motivation developed by participants based on the self-determined functional goals and the perceived usefulness of the therapy might help to maintain their treatment compliance. Indeed, a HABIT-ILE@home pilot study conducted in 3 adults with chronic stroke showed that the perspective of improving their motor control capacities, reaching their goals, and gaining autonomy was their main source of motivation, more than the playful nature of the therapy [54]. The daily program sent each day by the supervision team will aim to target the functional goals considered as important by the participant, thus supporting their intrinsic motivation.

In addition to the patients’ and caregivers’ motivation and adherence to treatment, a second aspect of the home-based protocol that needs to be documented is the burden of treatment. Indeed, caring for patients with chronic stroke may impose a significant burden on caregivers and could lead to heightened levels of anxiety and depression [59]. This affected mental health in caregivers can result in slower progress and poorer overall outcomes for the patient [60]. Moreover, the emotional state of caregivers and stroke patients is interconnected. Patients whose caregivers report greater burdens often exhibit higher levels of anxiety themselves, which could also impact patient improvements [59,61].

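### RCT1: 17 per group gives about 72% power, not 80%, under the two-tailed 0.05 test and the 95% CI rule that the protocol states; 80% needs 21 per group

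*Protocol article*

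**What the plan says.** The Sample Size section of the protocol article describes the RCT1 calculation as made "for a noninferiority 2-tailed" t test on the difference between two means. The SD comes from "the mean change observed after a CIMT intervention (+5.6 points at FMA-UE; SD 3.1"). The margin follows from the rule that home delivery "will be considered noninferior if the improvement produced is no more than 2.8 points lower than that obtained with the on-site HABIT-ILE intervention". Then "An α level of 0.05 and a 1-β level of 0.8 were used for calculation", and the "sample size calculation defined a number of 17 participants per group", or 34 in total. The planned true difference is not given, but the Discussion says "we anticipate similar improvements when comparing HABIT-ILE@home and HABIT-ILE on-site camp within the first RCT". The Study Design section gives "allocation ratio 1:1".

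The Statistical Analysis section for RCT1 sets the decision rule: "the 95% CI of the difference between groups will be computed", and noninferiority is concluded if its lower bound lies above the margin.

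The Sample Size section also raises recruitment to 48, allowing for about 30% attrition so that enough participants complete both phases.

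**The concern.** A noninferiority test has one tail that matters. The lower bound of a 95% interval is a one-sided test at 2.5%, and a two-tailed alpha of 0.05 puts the same 2.5% in that tail. The label in the Sample Size section and the rule in the analysis section therefore agree with each other. What does not agree with them is the number 17, which is too small for 80% power at the stated margin and SD.

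This is the primary comparison of RCT1. If power is lower than stated, a truly noninferior home programme is more likely to give an inconclusive interval, which may be misread as evidence against home delivery. Because 17 per group would reach 80% with a 90% interval, the mismatch also leaves room for an argument about the interval after the data are seen.

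**Working it through.** **Inputs.** Margin M = 2.8, SD s = 3.1, alpha 0.05, power 0.80, 17 per group (all from Sample Size); 1:1 allocation (Study Design); lower bound of a 95% interval (Statistical Analysis, RCT 1). True difference 0 is an assumption: it is not stated, but fits the similar improvements that the Discussion anticipates.

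**Formula.** For n per group, SE = s × √(2/n), df = 2n − 2 and noncentrality δ = M / SE. Power = P(T > t_crit), where T is noncentral t with df and δ, and t_crit is the upper 5% or 2.5% point of the central t.

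**Step 1: try to reproduce 17.**
- One-sided 0.05, n = 16: SE = 3.1 × √(2/16) = 1.096; δ = 2.8/1.096 = 2.555; t_crit (df 30) = 1.697; power 80.3%. So 16 per group suffices, and n = 17 gives 82.4%.
- One-sided 0.025 (two-sided 0.05): the smallest n reaching 80% is 21 (Step 2).

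The stated 17 is thus within one participant of the one-sided 5% answer and four short of the one-sided 2.5% answer.

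**Step 2: power under the stated rule (one-sided 0.025).**
- n = 17: SE = 3.1 × √(2/17) = 1.063; δ = 2.633; t_crit (df 32) = 2.037; power **72.4%**.
- n = 21: SE = 3.1 × √(2/21) = 0.957; δ = 2.927; t_crit (df 40) = 2.021; power **81.5%**.

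| Analysed per group | Total | One-sided 0.05 | One-sided 0.025 |
|---|---|---|---|
| 16 | 32 | 80.3% | 69.6% |
| 17 | 34 | 82.4% | 72.4% |
| 20 | 40 | 87.7% | 79.5% |
| 21 | 42 | 89.1% | 81.5% |
| 24 | 48 | 92.5% | 86.5% |

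**Step 3: does the method matter?** The normal approximation n = 2(z_α + z_β)² s²/M² gives:
- one-sided 0.05: 2 × (1.645 + 0.842)² × 3.1²/2.8² = 15.2, so 16;
- one-sided 0.025: 2 × (1.960 + 0.842)² × 3.1²/2.8² = 19.2, so 20.

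Power at 17 per group is then Φ(2.633 − 1.960) = 75.0%. The shortfall is smaller but remains.

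**Step 4: does the SD matter?** At one-sided 0.025, 17 per group reaches 80% only if the SD is about 2.83 or less. The protocol states 3.1.

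**Step 5: what the recruited number allows.** With 48 randomised, 24 per group, 21 per group at T1 means 42 of 48. That is a loss of at most 6, or 6/48 = 12.5%, spread evenly over the arms.

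**The case against.** Four points can be made for the plan.

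- **The origin of 17 is unknown.** A reader might infer that a one-sided 5% test was entered into the software. The documents do not support stating this as fact: the text says two-tailed, and one-sided 5% gives 16, not 17. This objection stands, but the shortfall does not depend on how 17 arose.
- **The wording is consistent.** Two-tailed 0.05 and a 95% interval imply the same error rate. This also stands. Deleting the two-tailed label would not cure anything; the number is what fails.
- **Attrition.** A reader might infer that RCT1 will run at 72% power because 30% loss from 48 leaves about 34. The documents do not support that. The 30% is set for completing both phases and is explained partly by the two-phase design, whereas RCT1 ends at T1, straight after two weeks of treatment. No T1 attrition figure is given, and 17 per group at T1 would require all the planned loss to occur before then. The plan also specifies intention-to-treat with multiple imputation, so the analysis set is not simply the completers, although imputation does not in general restore the information that dropout removes.
- **Limited harm.** With the 95% rule kept, the type I error is protected, and recruitment is over, so the sample size cannot change. This bears on how serious the error is, not on whether it exists.

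The power figures also rest on an FMA-UE SD from one CIMT study, while the Primary Outcomes section says that only the total motor score will be used. No SD is given for that score, so restated power must be marked as conditional.

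**Conclusion.** The statement that 17 per group gives 80% power is wrong at the protocol's own inputs. Under the two-tailed alpha of 0.05, and equally under the 95% lower-bound rule, power is about 72% (75% by the normal approximation), so the chance of missing true noninferiority at that number is about 28% (100 − 72.4 = 27.6) rather than 20%. Reaching 80% needs 21 per group, 42 in total.

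This rests on a margin of 2.8, an SD of 3.1 on FMA-UE, a true difference of zero and equal arms. A true deficit for home delivery would lower power further. The 72% belongs to the stated requirement of 17; the power RCT1 actually has depends on how many were assessed at T1, and it is at least 80% if that is 21 or more per group. It is an error in the stated calculation, not a threat to the validity of the noninferiority rule.

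**What to change.** Keep the 95% interval rule. In the Sample Size section, state that the RCT1 test is at one-sided 0.025 (equivalently two-sided 0.05) and that the planning assumption is a true difference of zero. Replace the claim of 80% at 17 per group with: about 72% at 17, 80% needs 21 per group (42 in total), and about 86.5% if 24 per group are analysed at T1. Mark all of these as conditional on FMA-UE and SD 3.1.

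Give power by the number assessed at T1, noting that at least 80% requires 42 or more of the 48 (21 per group), and say that the attrition allowance of about 30% refers to completion of both phases.

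Record the 95% interval as final before analysis, which the article still places in 2026. The change adds no participants and alters no analysis. Its only cost is a less favourable stated power.
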